### 2.3 Sample size calculation

Two-hundred and twenty-five individuals who meet the selection criteria for the study will be recruited. The estimated sample size needed is n = 63 participants per condition considering a moderate effect size (Cohen’s d = 0.5) for the difference between the active arms at post-intervention compared to the control group for the primary variable (i.e., FIQR score) with an alpha = 0.05 and 1-b power = 0.80. With an expected dropout rate of 20%–25%, the final sample size is estimated at 75 individuals per arm. The effect size used for the sample size calculation corresponds to the average effect size for multicomponent interventions in FM vs. control group (Nüesch et al., 2013). Previous RCTs evaluating the FIBROWALK intervention indicated effect sizes between d = 0.4 (Serrat et al., 2021a) and d = 1.83 (Serrat et al., 2020). Using as a reference previous studies of the group evaluating the effect of different non-pharmacological treatments in FM patients on blood values of immuno-inflammatory markers (Andrés-Rodríguez et al., 2019; Montero-Marin et al., 2020), it is estimated that a sample size of 40 subjects per arm will be sufficient to be able to detect changes in the evaluated variables.

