### 2.9 Other self-reported measures

- The *Patient Global Impression of Change (PGIC)* and the *Pain Specific Impression of Change* (PSIC) (Scott and McCracken, 2015) are measures to assess, respectively, self-perceived meaningful clinical change (on a 7-point Likert scale, from 1 = “Much better” to 7 = “Much worse”) in general or in the following specific domains: physical and social functioning, work-related activities, mood, and pain.

- Adapted version of Credibility/Expectancy Questionnaire (CEQ; Devilly and Borkovec, 2000). It is a 6-item questionnaire widely used to assess treatment expectancy as well as the credibility of the FIBRO-On and FIBRO-Out interventions. The first part of the CEQ comprises three items focused on therapy credibility (i.e., the extent to which the treatment appears a)logical and b) useful, and c) the confidence with which the treatment’s patient would recommend this one to a friend with the same health condition); and three more items evaluating expectations (i.e., the extent to which the patient thinks an improvement will happen as a consequence of the treatment; the extent to which the patient really feels that the intervention will reduce him/her symptoms, and the extent to which the patient really feels a symptom improvement will occur). After finishing the treatment, the patient’s opinion regarding the treatment received will be also gathered by using the second part of the CEQ which includes the same questions as in the first part of the CEQ but in past tense. The CEQ showed overall adequate internal consistency (α = 0.84–0.85) in a previous study in a similar clinical sample (Pérez-Aranda et al., 2019).

- An *ad hoc* item (i.e., *Have you experienced, during the course of the treatment, any unwanted symptom that you think might be directly or indirectly associated with the intervention?*) to check for the presence of adverse effects (e.g., headaches, dizziness, sleep problems, *etc.*) associated with the evaluated interventions. This measure has been used in a previous study (Pérez-Aranda et al., 2019) and will be administered both at 6-week and post-intervention assessments.

- Patients’ adherence evaluation to the FIBRO-On and FIBRO-Out programs. An *ad hoc* instrument (i.e., personal practice log) for the weekly recording of home practice will be developed to determine level of adherence to psychotherapeutic and therapeutic exercise recommended homework.

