#### 2.11.1 Analysis of clinical effectiveness

The primary effectiveness analysis will be conducted on an intention-to-treat (ITT) basis with the FIQR total score as a primary clinical endpoint (McCoy, 2017) and by linear mixed-effects regressions with restricted maximum likelihood (REML). REML accounts for the correlation between repeated measures for each individual and produces less biased estimates of variance parameters when using small sample sizes or unbalanced data (Egbewale et al., 2014). No imputation of missing data will be conducted, since it has been reported that multiple imputation is not necessary for all types of missing data (missing completely at random, missing at random, and missing not at random) before computing longitudinal mixed model analysis (Twisk et al., 2013). Unstandardized regression coefficients (B) and 95% confidence intervals (95% CIs) will be computed for the ‘group x time’ interaction between groups at 6-week, post-treatment and 6-month follow-up assessments. Cohen’s d will be calculated for each pairwise comparison, using the pooled baseline SD to weight the differences in the pre–post mean values and to correct for the population estimate (Morris, 2008). The rule of thumb for effect size interpretation will be the classical cutoffs for Cohen’s d of 0.20 = small, 0.50 = medium, and 0.80 = large. All secondary clinical endpoints will be analyzed using the same statistical procedure. Benjamini–Hochberg correction for multiple comparisons will be applied to control for false rate discovery (Glickman et al., 2014). All the analyses will be replicated using a “completers” approach including all participants who finished the study, and a per-protocol approach, taking into account only those patients who attended at least 75% of the sessions (9 out of 12).

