In addition, to assess clinical significance of the improvement on the primary outcome (FIQR), all the participants will be allocated into the categories of “responder” and “non-responder” by using the criteria of presenting at least a 20% reduction in the pre–post FIQR total score or not, respectively (Bennett et al., 2009). This classification will be used to compute the number needed to treat (NNT) for each treatment when compared to the others. The NNT refers to the estimated number of patients who need to be treated with a new proposed treatment (i.e., rather than the control comparison treatment) for one additional patient to benefit. A 95% CI for each NNT will be calculated. This index allows findings from RCTs to be more meaningful to clinicians. Furthermore, in order to explore potential predictors of treatment response in each intervention arm, t-tests and χ2-tests will also be performed to assess potential baseline differences in sociodemographic, clinical and physiological variables between responders vs. non-responders within the FIBRO-Out and FIBRO-On arms. Finally, baseline differences between participants who completed all study assessments and those who did not will also be evaluated (with *t* and *χ2*-tests) to detect any potential attrition bias.

The differences between FIBRO-On and FIBRO-Out on perceived clinical improvement (assessed with PGIC and PSIC) and on treatment expectation/opinion (i.e., with the CEQ) will be computed using χ^2^ tests and Student’s *t* tests, respectively.

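### The ordered 7-point PGIC and PSIC ratings are assigned a χ2 test which, read as the usual unordered test, ignores direction and gives up roughly 35–55% of the power of an ordinal test for small to moderate shifts

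*Protocol article*

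**What the plan says.** Section 2.9 describes PGIC and PSIC as measures of change rated "on a 7-point Likert scale, from 1 = “Much better” to 7 = “Much worse". PGIC covers change in general, and PSIC covers specific domains of functioning, work, mood and pain.

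Section 2.11.1 gives the analysis. It names one contrast, "The differences between FIBRO-On and FIBRO-Out on perceived clinical improvement (assessed with PGIC and PSIC"), together with treatment expectation or opinion on the CEQ, and says that these differences "will be computed using χ^2^ tests and Student’s *t* tests, respectively". PGIC and PSIC therefore get χ2 tests and the CEQ gets t tests. TAU is not named in that sentence.

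Three other places bear on the point:

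- Table 3 puts PGIC/PSIC under secondary outcome measures, at post-intervention only. Section 2.9 files them under other self-reported measures, and the secondary outcomes listed in the study objectives at the end of the Introduction do not include them.
- Section 2.11.1 also states: "All secondary clinical endpoints will be analyzed using the same statistical procedure". That procedure is the mixed model with a group-by-time interaction.
- Section 2.11 uses χ2 tests for categorical values at baseline. Nowhere does the article mention a trend χ2, an ordinal model or grouped categories for PGIC/PSIC.

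**The concern.** The stated target is perceived improvement, which has a direction. An unordered χ2 on a 2 × 7 table is unchanged if the seven labels are shuffled. It can report that two distributions differ, but not that one programme was rated better. It also spreads its sensitivity over 6 degrees of freedom when the difference of interest is a shift along one axis.

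The contrast affected is between two programmes that section 2.6.2 presents as nearly the same and that the note to Table 1 calls equivalent in content. Small to moderate shifts are therefore plausible, and that is where the unordered test loses most. At stake is a non-significant result on the patient's own rating of change that reflects the test rather than the data.

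The status of the measure is also unclear. If it is a secondary endpoint, as in Table 3, the general rule sends it to a repeated-measures model that cannot be fitted to a rating taken once without a baseline. If it is an ancillary measure, as in section 2.9, only the active-arm χ2 applies. The article supports both readings.

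**Working it through.** **Inputs from the protocol article.** Seven ordered categories (section 2.9). Seventy-five randomised per arm, with 20–25% dropout (section 2.3), leaves 75 × 0.80 = 60 down to 75 × 0.75 = 56 per arm. Alpha is 0.05, taken as two-sided. The only planning effect is d = 0.5, and it concerns the active arms against control on FIQR: "considering a moderate effect size (Cohen’s d = 0.5) for the difference between the active arms at post-intervention compared to the control group". No effect size is given for PGIC/PSIC or for FIBRO-On against FIBRO-Out.

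**The plan's own figure.** For FIQR, n per arm = 2 × (1.960 + 0.842)² / 0.5² = 2 × 7.85 / 0.25 = 62.8, so 63. This matches section 2.3 and supports the two-sided reading. No power figure is stated for PGIC/PSIC.

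**Assumptions.** The article gives no PGIC distribution. Four were assumed: bell-shaped (0.05, 0.12, 0.20, 0.26, 0.20, 0.12, 0.05), skewed towards better, uniform, and strongly skewed. The second arm is shifted on a latent normal scale by d. Each setting has 20,000 simulated trials, with empty categories dropped for the χ2 test and ties corrected for the Wilcoxon test.

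**Power, range over the four distributions:**

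| n per arm | d | Unordered χ2 | Wilcoxon | Share of power lost |
|---|---|---|---|---|
| 60 | 0.2 | 0.07–0.09 | 0.17–0.18 | 48–57% |
| 60 | 0.3 | 0.14–0.17 | 0.32–0.35 | 52–57% |
| 60 | 0.4 | 0.24–0.28 | 0.52–0.55 | 48–54% |
| 56 | 0.5 | 0.36–0.41 | 0.67–0.71 | 42–46% |
| 60 | 0.5 | 0.39–0.44 | 0.70–0.74 | 41–45% |
| 75 | 0.5 | 0.49–0.55 | 0.79–0.83 | 34–38% |
| 60 | 0.6 | 0.56–0.62 | 0.85–0.88 | 30–34% |
| 60 | 0.8 | 0.84–0.89 | 0.97–0.99 | 10–14% |

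The loss is 1 minus the ratio of the two powers. For the bell shape at n = 60 and d = 0.5 it is 1 − 0.430/0.742 = 42%. The linear-by-linear trend test performs about the same as Wilcoxon (0.69–0.76 at n = 60, d = 0.5). With no true difference and n = 60, the unordered χ2 rejected in 3.6–4.6% of trials, so it is slightly conservative as well.

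**A different shift model.** With category probabilities 0.08, 0.15, 0.22, 0.25, 0.15, 0.10, 0.05, 58 per arm and a proportional-odds shift, power is 0.28 against 0.55 at OR 2.0 and 0.48 against 0.78 at OR 2.5. The losses are 1 − 0.28/0.55 = 49% and 1 − 0.48/0.78 = 38%. About 26% of cells have an expected count below 5.

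**Analytic check.** A 1-df test has 0.80 power at noncentrality (1.960 + 0.842)² = 7.85. At that value a 6-df χ2 has power 0.52. To reach 0.80 it needs noncentrality 13.62, which is 13.62/7.85 = 1.74 times the sample.

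**Grouping.** If PGIC is split into improved or not, cutting at 2 or at 3, χ2 power at d = 0.5 and 60 per arm is 0.40–0.61, still below 0.70–0.74.

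**Where the ordinal test does worse.** Take the bell shape against a more spread-out distribution with the same centre (0.15, 0.12, 0.13, 0.20, 0.13, 0.12, 0.15). At 60 per arm the unordered χ2 has power 0.54 and Wilcoxon 0.05.

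**The case against.** The article says only that χ2 tests will be used. It does not say Pearson's test on seven categories, and a trend χ2 would lose essentially nothing. The exact form could sit in an analysis plan that is not shown. This stands as a limit on certainty. But the article does choose the test family and the contrast, and it uses χ2 for plain categorical data elsewhere, so the unordered test is the natural reading.

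The response distribution and the effect are assumed. A reader might infer that half the power is always lost, and the figures do not support that. The loss depends on the size of the effect, and it is modest if the two formats differ greatly. Section 1.1 itself notes apparently larger effects outdoors, so a large difference cannot be ruled out. The advantage of an ordinal test also requires a consistent shift.

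A reader might also infer from Table 3 that TAU ratings are collected and then left unused. The article does not support this. Table 3 restricts no row by arm: the CEQ, which section 2.9 ties to the two programmes, and therapist fidelity, which section 2.7 confines to FIBRO-Out, appear without restriction too. Nowhere is it stated that TAU participants complete PGIC or PSIC. Nor is meaningful change against TAU left unexamined, because section 2.11.1 classifies all participants by a 20% FIQR reduction and computes an NNT with 95% CI for each treatment against the others. This part of the objection stands in full.

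**Conclusion.** The choice of test should be changed. Read as the usual unordered χ2, it ignores the order that section 2.9 gives the scale. For a consistent shift of about d = 0.2–0.5 with 56–75 per arm, it loses roughly 35–55% of the power of an ordinal test. The loss is about half for d = 0.2–0.4, 34–46% at d = 0.5, and 10–14% at d = 0.8. These sizes rest on assumed response distributions, all seven categories being used, and a shift rather than a change in spread. The direction of the result does not depend on which of the four distributions is used.

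On TAU, the conclusion is narrower. Table 3, section 2.9 and the two statements in section 2.11.1 do not agree on what kind of endpoint PGIC/PSIC is or which analysis applies, and the article does not say whether TAU is assessed. They need reconciling. It does not follow that a planned comparison with TAU has been dropped. The measure is taken once, is outside the listed objectives and does not touch the primary conclusion, so the point is worth fixing but is not critical.

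**What to change.** In section 2.11.1, replace the χ2 test for PGIC and each PSIC domain, in the FIBRO-On against FIBRO-Out comparison, with an ordinal analysis. A proportional-odds model reporting the odds ratio with 95% CI is preferable because it gives direction and size. A Wilcoxon rank-sum or linear trend test is an acceptable alternative.

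State whether PGIC/PSIC is a secondary endpoint or an ancillary measure, align Table 3 with section 2.9, and exempt it from the mixed-model rule, which cannot apply to a single rating. State whether TAU participants complete it. If they do, add FIBRO-On against TAU and FIBRO-Out against TAU under the planned Benjamini–Hochberg correction.

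Cost: for the active-arm comparison, a change of wording only. The ordinal test is less sensitive to a pure difference in spread, so the full category counts by arm should be tabulated as well. Adding TAU brings up to two more contrasts per item. With PGIC and four or five PSIC domains, depending on how they are counted, that means 15–18 tests (5 × 3 to 6 × 3) instead of 5–6. If TAU is not currently assessed, these comparisons would need new data collection, and the correction asked for here does not depend on them.

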### 2.5 Procedure and randomization

The recruitment of participants will be carried out in two ways: 1) consecutive recruitment from consultation by the rheumatologists of the HUVH Central Sensitivity Syndromes Specialized Unit and 2) by screening a list of patients (with contact telephone number) corresponding to patients who contacted the Unit during the last 6 months. The clinicians involved in the project (i.e., MA and MS) will proceed to carry out the telephone screening and those who meet the selection criteria of the study will be invited to participate. After obtaining written informed consent, the instrument battery -including clinical and economic measures-described below will be administered (online assessment). Two research assistants will coordinate the study assessments to ensure an adequate understanding of all administered self-reported measures. Random assignment of participants to study arms will be executed after baseline assessments as recommended by the CONSORT guidelines (Schulz et al., 2010). Once written consent and baseline assessment have been completed, study participants will be given a unique personal code and randomized using randomization software (1:1:1 ratio). The computer-generated randomization will apply a permuted block design to ensure that the groups are balanced taking biomarkers substudy eligibility criteria (No=Not meeting criteria for biomarkers substudy; Yes = Meeting criteria) into account. The randomization list will be stored in an encrypted file on a password-protected computer in the clinical trials supervisor’s office to assure concealment of allocation. Participants will be informed of their group allocation by the administrative personnel, who will send a notification *via* email.

Patients who meet the selection criteria for the biomarkers substudy will be rescheduled 3–5 days after the first assessment to obtain blood samples (up to the required N of 40 subjects per arm). Fasting blood extractions will be performed in a pre-set time window (8a.m.–10a.m.) to reduce circadian variability in the levels of the biomarkers evaluated. In order to limit the effects of medication on the study variables, patients will be asked to refrain from taking any occasional anti-inflammatory drugs in the 72 h prior to blood sampling.

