### 2.13 Blinding

Randomization and group allocation will be completely masked for the study assessors and study participants will be asked not to communicate with the assessor about the treatment received. The study participants will be provided with a summary of evidence of the FIBROWALK program which constitute the basis for FIBRO-On and FIBRO-Out programs. As it is usual in non-pharmacological trials, neither participants nor the therapists can be blinded to treatment allocation. The therapists in the FIBRO-On and FIBRO-Out arms will not be involved in any assessment task of the study.

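### The expectancy part of the CEQ is completed before randomisation, so the planned FIBRO-On versus FIBRO-Out test on expectation can show only chance imbalance

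*Protocol article*

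**What the plan says.** Four statements in the protocol article bear on this point.

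- **Instrument (section 2.9).** The CEQ is described as "widely used to assess treatment expectancy as well as the credibility of the FIBRO-On and FIBRO-Out interventions". It has a first part on credibility and expectation. A second part, given after treatment, puts the same questions in the past tense about the treatment received.
- **Schedule (Table 3, section 2.8).** The CEQ is marked at baseline and at post-intervention (12 weeks). No time point lies between allocation and the start of treatment.
- **Order of events (section 2.5).** "Random assignment of participants to study arms will be executed after baseline assessments as recommended by the CONSORT guidelines". The same section repeats the order: "Once written consent and baseline assessment have been completed, study participants will be given a unique personal code and randomized". Only afterwards is the arm disclosed: "Participants will be informed of their group allocation by the administrative personnel", by e-mail.
- **Analysis (section 2.11.1).** The two active arms are compared "on treatment expectation/opinion (i.e., with the CEQ) will be computed using" Student's t tests; the chi-square tests in the same sentence belong to the impression-of-change scales.

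**The concern.** A between-arm test of expectancy is useful if patients know what they are about to receive when they answer. On this schedule they do not. A patient who will be sent to the park and one who will be sent videos answer under identical information, so any preference that appears once the arm is known cannot enter the score.

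The risk is one of interpretation. The primary outcome, the FIQR, is self-reported. Section 2.13 states that participants cannot be blinded and also that "The study participants will be provided with a summary of evidence of the FIBROWALK program". Section 1.1 reports apparently larger effects for the outdoor format and presents the comparison of formats as a knowledge gap that the study will address. Format-specific expectancy is thus a plausible rival explanation for a difference between FIBRO-On and FIBRO-Out. A non-significant baseline CEQ test could easily be taken as evidence against that explanation, although it carries no information on it. No later analysis plan can repair this, because a score taken after allocation and before treatment would not have been collected.

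**Working it through.** **1. The plan's own figures.** The article gives no effect size, SD or power for the CEQ. The nearest figure is the sample size in section 2.3: d = 0.5, alpha = 0.05 (two-sided assumed), power 0.80. The formula n = 2(1.960 + 0.842)² / 0.5² = 2 × 7.85 / 0.25 = 62.8 gives 63 per arm, which reproduces the stated 63. The check below uses the planned 75 per arm, and 75 × 0.75 = 56.25, so 56 per arm at the upper end of the stated dropout range.

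**2. What randomisation implies.** Let X be the CEQ score given before allocation and A the arm. A is drawn after X is recorded, so A is independent of X (within the biomarker-eligibility strata used for blocking). Hence E[X | FIBRO-On] − E[X | FIBRO-Out] = 0 among all randomised patients. The null hypothesis of the t test is true by design, and its rejection rate is its type I error rate, about 5%.

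**3. Size of what is lost.** Suppose that knowing the arm would shift mean expectancy by δ SD between formats. The values of δ are assumptions. The table gives rejection rates from 20,000 simulated trials per row (two-sample t test, two-sided 0.05). In the pre-allocation column δ cannot enter, by construction.

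| Assumed δ (SD) | Before allocation, 75 per arm | After allocation, 75 per arm | After allocation, 56 per arm |
|---|---|---|---|
| 0 | 4.8% | 4.8% | 4.9% |
| 0.3 | 5.0% | 44% | 34% |
| 0.5 | 4.9% | 86% | 75% |
| 0.8 | 4.9% | 99.8% | 99% |

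Hand check of one cell: δ√(n/2) = 0.5 × √37.5 = 3.06, and Φ(3.06 − 1.96) = Φ(1.10) ≈ 0.86, which agrees.

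**4. The post-intervention part.** This score is taken after randomisation and concerns the treatment received, so it can differ by arm. By then patients have had 12 weeks of treatment and know how they have fared. A difference may reflect the result obtained as much as what was expected beforehand.

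**The case against.** The strongest reply is that the article does not describe exactly how the adapted CEQ is given. Patients receive an overview of the interventions before consent (section 2.12), so each might rate both formats at baseline. A paired t test of those ratings would be informative. Also, the baseline column of Table 3 is not a single moment, because baseline blood is drawn 3–5 days after the first assessment. Neither possibility is stated for the CEQ. Section 2.5 mentions later timing only for blood, and section 2.11.1 describes a difference between FIBRO-On and FIBRO-Out without mentioning pairing. If patients do rate both formats, a between-arm test is still the wrong comparison. Completion before allocation therefore remains the natural reading, though the full protocol could settle it.

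Three stronger inferences are tempting, and the document does not support them.

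- **That the trial cannot check its main source of bias from lack of blinding.** The article gives the CEQ no such role. It sits among other self-reported measures, and lack of blinding is acknowledged as a limitation in section 3. Calling expectancy the main source would be a judgement. No CEQ comparison with TAU is planned, so re-timing would not change what is known about expectancy in the comparisons with control for which the trial is powered.
- **That the whole CEQ comparison is empty.** Only the expectation half is; the opinion half can differ by arm.
- **That a null baseline result is guaranteed.** It is about 95% likely.

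It is also fair to say that no primary or secondary endpoint depends on the CEQ, that the article nowhere says a null result would be reported as equal expectations, and that the 5% figure merely restates alpha. The last point is the defect itself: the test has no other property.

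**Conclusion.** The point holds in a limited form. On the stated schedule, the FIBRO-On versus FIBRO-Out t test on expectation compares randomised groups on a score given before allocation. It can show only chance imbalance, with about 5% rejection whatever the true format-specific difference, and must not be read as evidence of equal expectations. The post-intervention part is a legitimate comparison of opinion but not a measure of pre-treatment expectancy.

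The conclusion rests on two readings: that the first CEQ part belongs to the baseline assessment that precedes randomisation, and that the t test is between arms. The power figures for a re-timed questionnaire (34% to 99.8%) rest on assumed shifts of 0.3 to 0.8 SD and show scale only. This is a correctable weakness in a supporting measure; the primary analysis is unaffected.

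**What to change.** - Give the first CEQ part online after the allocation e-mail and before session or module 1, worded for the assigned format.
- Keep it outside the blinded assessors' role. The administrative staff who send the allocation notice could send the link, so that masking is preserved.
- Show it as its own time point in Table 3, state the timing in section 2.9, and name that score in section 2.11.1 as the basis of the expectation comparison.
- If the timing cannot be changed, drop the between-arm test of the pre-randomisation CEQ. The score could still be described or used as a baseline predictor of response.
- In either case, label the post-treatment CEQ comparison as opinion only.

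The cost is one short online contact of six items, with no extra visit. A few responses may be missing, so response counts should be reported by arm.
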